### Research group and intervention

1. In this experiment, Wuhan Ired MagTD 60 magnetic stimulator will Be used, The stimulation coil will select a circular coil, and The stimulation parameters will Be selected As follows: the stimulation frequency will choose 20HZ, The intensity will select 80–120% resting motion threshold (RMT), The stimulation time will last for1s, The interval will last for9s, and a total of 20 Min will Be stimulated once a day, 5 times a week for 2 weeks.

Group A: in the sham stimulation group, subjects will remain in a supine position, and the stimulation coil will be chosen to be a circular coil with the stimulation site 2 cm in front of the vertex, which is not discharged, and another “8” coil rotated and placed under the subject’s pillow to avoid scalp stimulation (34).

Group B: rTMS of Bilateral M1, The patients will beseated or supine, wore anatomic positioning caps, and selected M1 region according to the international EEG 10–20 system (25), and the handle willpointed to the anteromedial aspect of the sensorimotor cortex on one side, the neck will beimmobilised to avoid head movement and the coil was placed close to the scalp with the central stimulation point tangential to the scalp. To ensure the accuracy of the MS site, the patient’s RMT will be determined by a single manual stimulation, and alternating left and right stimulation was given for 10 min each according to the stimulation parameters.

Group C: rMS of S3 nerve root, the patient will beplaced in prone position, and the stimulation site will select the S3 nerve root region (about the midpoint of the upper sacral edge and the tailbone line to the left and right). The center of the coil will be as close to the surface of the sacrum as is appropriate. Stimulation will be determined by bilateral toe movements or pronounced anal contractions (35), identified as RMT, and then rMS will be given based on the stimulation parameters.

Group D: dual-target stimulation of bilateral M1 and S3 sacral nerve roots will be performed at the same time.

2. All four groups of patients will be given bladder care and conventional rehabilitation treatment. Bladder care: ① Drinking plan: patients will berequired to have a daily fluid intake of 1,550–1,650 mL, not exceeding 2,000 m l, and evenly distributed between 8:00–20:00 (drinking once every 2 h), including the amount of fluid flow and the amount of intravenous fluid input. ② Intermittent clean catheterization (36): each catheterization will be preceded by self-catheterization, and if it is not possible or there is residual, then catheterization will be performed. The frequency of intermittent catheterization is decided according to bladder capacity and residual urine volume, up to 6 times per day. Conventional rehabilitation treatment: ①Bladder function training (37): finger tapping on the suprapubic area to find the trigger point, and for patients who cannot find the trigger point, uniform Percussion on the bladder area 2–3 cm above the pubic symphysis, 50–100 times/min, 2–3 min percussion each time. ②Acupuncture treatment Acupuncture treatment will be performed by an experienced Chinese medicine practitioner who has been practicing acupuncture for more than 5 years, selecting the points Shangxing, Baihui, Qihai, Guanyuan, Zhongji, Baxiao, Double Large Intestine Yu, Double Kidney Yu, Double Guanyuan Yu, Double Bladder Yu, Double Chichibian, Double Huanjiu, Double Chengfu, Double Huizhong, Double Ashigangsanli, Double Sanyinjiao, Double Yinlingquan, Double Fenglong, Double Hangzhong, Double Kunlun, and clean and disinfect each point; and then needle the acupuncture points and leave the needles for 30 min. The treatment will be performed once a day for 30 min, 5 times a week for 2 weeks.

## Outcome measures

Outcome measures will be evaluated at 1 day before intervention and 2 weeks after the start of treatment. All evaluations will be conducted by the same uninformed therapist and rehabilitation physician.

### Primary outcome

The most important evaluation index is the residual urine volume of the bladder, the residual urine volume of the bladder can intuitively show the improvement of the urination function of patients with urinary retention. The main way is to measure the residual urine volume of the urinary system color ultrasound of the four groups of patients on the first day of treatment and the first day after treatment. Prior to the examination, the patient first attempts to empty the urine without external force or manipulation, and then a urinary ultrasound will be performed immediately. During the examination, the patient will be asked to lie flat on their back with the probe located in the midline above the pubic symphysis. Each measurement will scan the bladder in both the sagittal and transverse planes and measure the bladder capacity at this point to get an idea of the patient’s residual urine volume. The smaller the residual urine volume, the lower the degree of urinary retention.

### Secondary outcomes

#### Urination diary

The urination diaries will bea secondary outcome of this study. The urination diaries of 3 days before and after treatment will be recorded in this study. When recording the urination diary, it will berequired to ensure that the recording duration of a day is continuous for is 24 h, and to ensure the accuracy of the diary. The fluid intake will berecorded in units accurate to milliliters, and the volume of urine would measurusing a professional urine measuring tool to demonstrate the accuracy of the urination diary. The overall improvement of urinary catheterization times, voiding times, voiding volume and residual urine volume in the four groups for 3 consecutive days before and after treatment will beevaluated, and the mean value was calculated. In patients with urinary retention, the number of catheterizations decreased, the number of urination increased, and the volume of urination and residual urine increased, indicating that the symptoms of patients improved more significantly.

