## Eligibility criteria

### Inclusion criteria

Participants who met all of the following criteria willbe considered for inclusion: (1) met the classification criteria for SCI in the International Standard for Neurological Classification of SCI (32) and were confirmed by MRI or CT; (2) clinically present with varying degrees of urinary retention, i.e., residual urine volume > 100 mL after bladder emptying; (3) aged 18–60 years, regardless of gender; (4) patients graded B, C, or D according to the American Spinal Cord Injury Association functional rating criteria (ASIA); (5) had a disease duration between 1 month and 2 years and underwent intermittent catheterization; and (6) voluntarily participatingin this study and signingan informed consent form.

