### Sample size calculation

According to published literature (33) the mean post-intervention residual urine volume in the four groups A, B, C, and D were expected to be 302.6, 56, 107.2, and 179, respectively, with a standard deviation of 160.4. The degree of certainty 1−β = 0.90, test level *α* = 0.05, group A:B:C:D = 1:1:1:1 and sample size estimation will be performed using PASS 15 software according to the following equation.

$$n=\Psi^{2}\left[\overset{k}{\underset{i=1}{\sum }}{s_{i}}^{2}/k\right]/\left[\overset{k}{\underset{i=1}{\sum }}{\left({\bar{X}}_{i}-\bar{X}\right)}^{2}/\left(k-1\right)\right]$$

According to the predefined parameters, the minimum required samples for groups A, B, C and D were all 12 cases after the calculation of residual urine volume using One-Way Analysis of Variance F-Tests under the Means menu of PASS 15 software. Considering the lost rate of 20%, it is expected that 15 cases will be included in groups A, B, C, and D in this study, and a total of 60 cases will be included, which can ensure the accuracy and scientific accuracy of the study results.

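### The urination diary section gives the wrong direction of benefit for residual urine, one of its four components, and so contradicts the primary outcome

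*Protocol article*

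**What the plan says.** The Urination diary section (Secondary outcomes) describes a record kept for 3 days before and 3 days after treatment, with mean values calculated. It names four components: "The overall improvement of urinary catheterization times, voiding times, voiding volume and residual urine volume in the four groups". It then says which changes count as improvement in patients with urinary retention. For the first two components, the favourable pattern is that "the number of catheterizations decreased, the number of urination increased". For the other two, the sentence continues: "the volume of urination and residual urine increased, indicating that the symptoms of patients improved more significantly".

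The Primary outcome section also uses residual urine volume, measured by ultrasound, and gives its direction: "The smaller the residual urine volume, the lower the degree of urinary retention".

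Two further places bear on the direction:

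- The Inclusion criteria admit patients who "clinically present with varying degrees of urinary retention, i.e., residual urine volume > 100 mL after bladder emptying".
- The Sample size calculation says that mean post-intervention residual volumes in groups A (sham), B, C and D "were expected to be 302.6, 56, 107.2, and 179, respectively, with a standard deviation of 160.4".

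**The concern.** Residual urine volume is both the primary outcome and a component of the first secondary outcome, and the two sections give it opposite directions of benefit. The diary sentence is the only statement in the article of what counts as improvement on the diary. The Discussion presents the diary as a fuller picture of how urination has improved, so it is meant to support the primary result.

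If the sentence is followed as printed, an arm whose residual urine falls is credited with benefit on the primary outcome and marked down on the matching diary component. A treatment that works would appear to give conflicting primary and secondary evidence. A treatment that worsens emptying would gain apparent support from the diary.

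**Working it through.** The point concerns direction, so the main check sets the relevant statements side by side. A short calculation then shows which direction the design relies on.

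**Direction of residual urine in each section of the protocol article**

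| Section | Statement | Favourable direction |
|---|---|---|
| Urination diary | "the volume of urination and residual urine increased, indicating that the symptoms of patients improved more significantly" | Increase |
| Primary outcome | "The smaller the residual urine volume, the lower the degree of urinary retention" | Decrease |
| Inclusion criteria | Retention is "residual urine volume > 100 mL after bladder emptying" | Decrease (a high residual defines the condition) |
| Sample size calculation | Sham 302.6; active groups 56, 107.2 and 179 | Decrease (all active groups below sham) |

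The diary section stands alone against the other three. In its sentence a single verb governs both voided volume and residual urine, so there is no natural reading in which one rises and the other falls.

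**Consistency within the diary section.** The bladder-care text under Research group and intervention makes the frequency of intermittent catheterisation depend on bladder capacity and residual urine volume. The diary sentence counts fewer catheterisations and more residual urine together as improvement, although residual urine is one of the things that determines how often catheterisation is done. The directions given for catheterisations, voids and voided volume are all consistent with less retention. Only the residual urine component is out of line.

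**What the sample size relies on.** The inputs, all from the Sample size calculation, are means of 302.6, 56, 107.2 and 179, SD 160.4, four equal groups, alpha 0.05, "The degree of certainty 1−β = 0.90" and 20% loss.

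- Grand mean: (302.6 + 56 + 107.2 + 179) / 4 = 644.8 / 4 = 161.2.
- Sum of squared deviations: 141.4² + (−105.2)² + (−54.0)² + 17.8² = 19993.96 + 11067.04 + 2916.00 + 316.84 = 34293.84.
- Noncentrality for n per group: λ = n × 34293.84 / 160.4² = n × 34293.84 / 25728.16 = 1.333n.
- Power of the one-way F-test, with 3 and 4(n − 1) degrees of freedom: 0.879 at n = 11 and 0.910 at n = 12. The minimum is 12 per group, as stated.
- Allowing for loss: 12 / (1 − 0.20) = 15 per group, and 4 × 15 = 60 in total, as stated.

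The stated figures reproduce. The F-test has no direction, so they do not depend on how the diary sentence is worded. The means behind them do assume that successful treatment lowers residual urine.

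**Effect on the planned tests.** The Statistical analysis section lists t tests, one-way ANOVA, rank sum tests and chi-square tests, none with a stated direction. Correcting the sentence would leave every estimate and p-value as it is. Only the label attached to a rise or fall in diary residual urine would change.

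**The case against.** The strongest reply is that this is a drafting or translation slip with little practical effect. Every other statement in the article on the matter points the right way, a clinician would probably notice the anomaly, and no planned analysis uses the sentence. The article describes no diary composite, signed score, responder definition or ranking of arms. Most of this stands, and it limits the size of the point. It does not remove the point, because the sentence is the only published rule for reading this component and nothing elsewhere in the article corrects it.

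A reader might go further and infer either of two things that the document does not support:

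- **That the diary endpoint as a whole would be read backwards.** Three of the four components have coherent directions, and the diary is one of several secondary outcomes.
- **That the diary rule would rank sham as the best arm, because its planning mean is the highest.** The planning means are expected post-treatment levels of the primary outcome, not diary values. The diary sentence is about change and gives no rule for ranking arms on levels.

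**Conclusion.** The diary section is wrong as written on one point: it gives the wrong direction of benefit for residual urine, one of four diary components. It contradicts the Primary outcome section outright, and it runs against the inclusion criterion and the planning means.

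The effect is confined to interpretation. The sample size of 12 per group, 15 after losses and 60 in total is unaffected, and so are the planned tests and their p-values. What could go wrong is the conclusion drawn from that component, where the same fall in residual urine would be read as harm in the diary and benefit on the primary outcome.

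The conclusion assumes that residual urine means the same thing in the diary and in the primary outcome. The article uses the same term in both places and gives no reason for the diary value to run the other way. The correction should be made before results are read, although the point is modest in scale.

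**What to change.** Rewrite the sentence so that residual urine is separated from voided volume. For example: in patients with urinary retention, fewer catheterisations, more voids, larger voided volume and smaller residual urine indicate improvement. This agrees with the Primary outcome section and keeps the article's own four components. The 3-day recording and the averaging are already described and need no change.

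The cost is one sentence. Data collection, sample size, planned tests and patient care are all unaffected.

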#### Functional brain imaging techniques

In this study, we will collecte the fNIRS data with a 37-channel device (BS-3000, Wuhan Zilian Hongkang Technology, Wuhan, China), and will use BrainScope software to display and save the fNIRS data. The data will be processed by Wuhan Yiride Medical Equipment Co., LTD, and the average concentration changes of oxy-hemoglobin (HbO2), Deoxy-hemoglobin (HbR) and Total- hemoglobin (HbT) in each channel of subjects in each group will be calculated. Before the experiment, the patients will be asked to sit in a chair, and the light source and detector will be placed on the head and close to the scalp of the patients. The signals will be mainly collected in the primary motor area (M1), pre-motor area and auxiliary motor area, in which channel 19 will beused as the Cz reference point, and the left and right cerebral hemispheres were distributed symmetrically, As shown in Figure 2. The main detection indexes were the content of HbO2, HbR, and HbT. Participants will berequired to keep quiet during the test without any movements (29). The block design was adopted: the resting period was 25 s and the task period was 15 s. Considering the need for subjects to acclimatize to the detection environment and to ensure that the fNIRS signal reaches a steady state, 25 s of baseline resting data will be collected before proceeding to the task period. The resting period and the task period will be repeat for 5 times, and then the resting data of 25 s will be collected after the end, for a total of 225 s. Resting period (25 s): 25 resting periods in which participants rest without any movement. Task period (15 s): complete the “anal lift” 3 times within 15S according to the operator’s suggestion (the “anal lift” movement is guided by the pelvic floor rehabilitation therapist before the test).

**Figure 2 fig2:**
[figure not shown]
Channel layout diagram.

### Glazer pelvic floor surface electromyography (sEMG) assessment

Glazer pelvic floor sEMG assessment is the gold standard for evaluating pelvic floor muscle function, which can evaluate pelvic floor muscle support function, sexual function and sphincter function to understand the effect of pelvic floor muscle rehabilitation. The pelvic floor EMG values will be measured on the first and last day of treatment: before the assessment, the patient will be placed in a comfortable and relaxed position, in a truncated position, with the upper and lower body at a certain angle (about 120°), and the feet were naturally externally rotated to avoid the interference of the contraction of the intrapelvic muscles with the pelvic floor EMG signal. The electrodes will beplaced in the vagina (or anus) with metal pieces touching the pelvic floor muscles on the left and right sides to collect pelvic floor surface myoelectricity; the abdomen will beplaced under the umbilicus with disposable body electrode pieces to detect the force of abdominal muscles and avoid abdominal muscle compensation.

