### Randomization and blinding

Randomization of included patients based on length of stay will be performed using the random number table method. Throughout the study, all investigators and subjects will be unaware of the allocation of interventions, Outcome evaluators and data analysts will be blinded, and subjects will be randomly assigned to groups by persons unrelated to the trial. Opaque closed envelopes containing sequence numbers used for allocation concealment will be identified with different numbers. Once the sequences is generated, the envelopes will be placed in a secure place in numerical order and the paper containing the corresponding group information will be placed in the envelopes. Sequence generation and production will be performed by rehabilitation physicians not involved in this study.

An experienced blinding rehabilitation physician or therapist will perform an initial assessment of enrolled patients and an assessment after 2 weeks of treatment. In the event of a serious adverse event, emergency unblinding will be performed and the involved subject will be removed from the trial protocol. When the experiment is complete, the statisticians will have four sets of data.

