### Statistical analysis

All data will beanalyzed using SPSS 21.0 statistical software. The measures will beexpressed as mean ± standard deviation (
$\bar{x}$
±SD), and one-way analysis of variance (ANOVA) or chi-square test will be used in all demographic characteristics and baseline assessments, The primary and secondary outcome measures will be expressed as 
$\bar{x}$
±SD, and the data will be tested for a normal distribution. Before and after treatment, the uniformity of variance data between the two groups will be analyzed using *t* test. If the data is skewed, it will be converted to normal distribution according to the data distribution type; If the data does not conform to any distribution law, the rank sum test will be used to test the hypothesis of the data. Data with abnormal distributions or uneven variances will be analyzed using Wilcoxon rank sum tests. *X*^
**2**
^ test was used for counting data, and *p* < 0.05 for all tests was considered statistically significant.

The fNIRS data will beprocessed by professional data analysts of Wuhan Ired Medical Equipment Co., LTD. SPSS 21.0 will beused for data analysis to calculate the differences in activation intensity of each brain region, and the average concentration changes of HbO2, HbR, and HbT in each channel of subjects in each group will becalculated. Paired sample *t* test will beused to investigate the differences in blood oxygen changes before and after treatment, and one-way analysis of variance will be used for comparison between groups. *p* ≤ 0.05 will beconsidered as a statistically significant difference.

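### Pelvic-floor sEMG may be recorded vaginally or anally, with no rule holding a patient to one route and no route or baseline term in the stated comparison: a minor loss of precision and consistency on one secondary outcome

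*Protocol article*

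**What the plan says.** All references are to the protocol article.

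- **Glazer sEMG section, route:** "The electrodes will beplaced in the vagina (or anus) with metal pieces touching the pelvic floor muscles". The section also sets body angle, foot position and the abdominal reference electrode. It gives no rule for which route a woman receives.
- **Glazer sEMG section, timing:** "The pelvic floor EMG values will be measured on the first and last day of treatment". It does not say that the second recording uses the same route as the first.
- **Inclusion criteria:** patients are "aged 18–60 years, regardless of gender". Men can only be recorded anally, so route is tied to sex. The expected sex mix is not given.
- **Statistical analysis:** one paragraph serves all outcomes. "The primary and secondary outcome measures will be expressed as" mean ± SD, followed by a t test, or by transformation or a rank-sum test where the assumptions fail. For sEMG it names no route, sex or baseline term.
- **Randomization and blinding:** allocation "will be performed using the random number table method", with no stratification by sex mentioned. The ratio is "group A:B:C:D = 1:1:1:1".

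**The concern.** Electrodes in two different cavities need not give amplitudes on one scale, and the protocol neither normalises the readings nor argues that they are comparable. If the scales differ, there are three consequences.

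1. Raw sEMG values vary more within each arm, because each arm mixes two kinds of recording.
2. In arms of 12 to 15 patients, the share of vaginal recordings will differ by chance, and that difference enters the arm contrast.
3. If a woman is recorded by different routes on the two days, the switch appears in her before-after difference as if it were a treatment effect.

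The third matters most for the assessment procedure. If route is neither held nor recorded, no later analysis can reliably repair it.

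**Working it through.** **The plan's own figure.** The Sample size calculation gives means of 302.6, 56, 107.2 and 179, SD 160.4, α = 0.05 and power 0.90.
- The grand mean is 161.2 and the sum of squared deviations is 34,293.84.
- With n = 12 the noncentrality is 12 × 34,293.84 / 160.4² = 16.0, and power is 0.910. With n = 11 power is 0.879.
- So 12 per arm is right, and 12 / 0.80 = 15 per arm, 60 in all.

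The figure reproduces, but it concerns residual urine volume. The protocol gives no figure for sEMG.

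**Assumptions for sEMG (none is in the document).** The share of vaginal recordings p is 20% to 50%. The mean difference between routes d is 0.5 to 1.0 within-route SD. There are 12 evaluable patients per arm, or 15 where stated.

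**Expected bias.** Allocation is random, so the expected difference in route mix between arms is zero. In 40,000 simulated four-arm trials per setting (15 per arm, no treatment effect, d = 0.5 to 1.5, p = 25% or 50%), with route ignored, the type I error of the ANOVA or t test was 0.047 to 0.051.

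**Variance of raw values.** Inflation factor = 1 + p(1 − p)d².
- p = 0.2, d = 0.5: 1 + 0.16 × 0.25 = 1.04.
- p = 0.5, d = 1.0: 1 + 0.25 × 1 = 1.25.

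**Chance imbalance between two given arms (p = 0.25, n = 12).**
- SD of the difference in share = √(2 × 0.25 × 0.75 / 12) = 0.177.
- Mean absolute difference ≈ 0.177 × √(2/π) = 0.14, or 14 percentage points. The exact binomial value is also 0.14.
- Typical shift of the contrast = 0.14 × d = 0.07 SD (d = 0.5) to 0.14 SD (d = 1.0).
- Standard error of an arm difference at n = 12 = √(2/12) = 0.41 within-route SD.

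**Larger gaps.** With 15 per arm, two given arms differ by at least 20 points in 25% to 36% of trials (p from 20% to 50%). That gap shifts the contrast by 0.2 × d = 0.10 to 0.20 SD. Among simulated trials with such a gap (p = 25% or 50%), the t test's type I error was about 0.06 at d = 0.5 and 0.08 at d = 1.0.

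**Change of route within a patient.** If the difference is additive and the route stays the same, it cancels in that patient's before-after change. A multiplicative difference would not fully cancel. If the route changes, the whole of d enters her change. One such patient in an arm of 12 moves that arm's mean change by d/12, which is 0.5/12 = 0.04 to 1.0/12 = 0.08 SD.

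**The case against.** The case against acting is strong on several counts.

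- **Confounding.** A reader might infer that arm differences in sEMG systematically reflect electrode route and sex mix. The document does not support that. Allocation is random, chance imbalance is already part of the error that the test allows for, and the overall type I error is nominal. This objection stands in full.
- **The scale difference is not documented.** The Glazer section describes the electrode as touching the pelvic floor muscles whichever route is used. If the routes differ little, the effect is close to nil. This also stands: every size above rests on an assumed d.
- **The worst pair of arms is not the typical contrast.** At p = 25% and n = 12, the gap between the highest and lowest of four arms averages about 25 points and reaches 25 points in about 63% of trials. Quoting that would overstate the shift. The gap between two given arms averages about 14 points.
- **Pooling and switching are inferred.** The analysis paragraph is generic and does not say that the two kinds of reading are combined. A covariate could sit in a statistical analysis plan that is not shown, and the choice of route may simply follow anatomy. This stands in part. The tests that the article does name have no place for route or baseline, and nothing in the stated procedure keeps route constant. No text suggests that switching is intended.
- **One route for everyone.** Using the anal route in all patients looks like a clean solution, but it trades comfort for some women, and possibly the choice of muscle recorded, against uniformity. The document gives no basis for preferring it.

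**Conclusion.** The point holds as a minor matter of precision and measurement consistency on one secondary outcome. The article allows two recording routes in a mixed-sex trial, leaves the route free between visits, and names a comparison that uses neither route nor the baseline sEMG already collected.

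There is no expected bias. If the routes differ by 0.5 to 1.0 within-route SD, raw variance rises by about 4% to 25% (20% to 50% vaginal recordings). A given arm contrast typically shifts by 0.07 to 0.14 SD (25% vaginal, 12 per arm), about a sixth to a third of its standard error of 0.41 SD. Both the route difference and the sex mix are assumptions. A route change within a patient would be a real measurement error, but how often it would happen is unknown. Neither the primary outcome nor the sample size is affected.

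**What to change.** **Glazer sEMG section:** state that each patient's electrode route is set at baseline, that the same route is used at the post-treatment recording, and that the route is recorded at both.

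**Statistical analysis:** for sEMG, replace the t or rank-sum comparison with a linear model of the post-treatment value across the four arms, with baseline sEMG and route as covariates.

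**Cost:** a sentence in the procedure, one extra data field, and about one degree of freedom for route. Baseline sEMG is already collected, so no assessment is added. Because an unrecorded route cannot reliably be recovered later, the procedural sentence is the more pressing of the two.
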